Our study aims to add to the development of treatment strategies for adolescents and to the evidence base of treatment approaches. The study will furthermore investigate predictors and moderators of treatment response. This report presents Version 6 (20 December 2016) of the study protocol. We followed the Standard Protocol Items Recommendations for Interventional Trials (SPIRIT) Statement 2013 (see Additional file 1: SPIRIT 2013 Checklist: recommended items to address in a clinical trial protocol and related documents). For the complete World Health Organization Trial Registration Data Set, please see Additional file 2.

Our primary hypothesis is a significantly greater reduction in the primary outcome (ADHD symptoms) in the IMTP group compared to the active control condition TASH. On secondary outcomes such as global impairment, internalising and externalising symptoms, we expect greater benefit in the IMTP group compared to TASH, whereas parenting is expected to improve more in the parent-focused TASH group. We expect treatment effects and group differences to remain stable at follow-up.

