### Primary and secondary outcome measures

#### Primary outcome

The primary endpoint is the change in ADHD symptoms from T2 to T3 measured by changes in the total score of the Diagnose-Checkliste für Aufmerksamkeitsdefizit−/Hyperaktivitätsstörungen (DCL-ADHS), a structured DSM-5-based clinical interview. It comprises 18 items assessing ADHD symptoms, and five items assessing functioning and psychological strain and shows good internal consistency (Cronbach’s α = 0.89–0.95) and high validity [52–54]). All items are rated on a 4-point scale (0–3; symptom present if ≥2). For ESCAadol, the interview is conducted with parents and adolescents in a joint session.

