### Proposed sample size and power calculations

The calculation of the sample size (software: STPLAN Version 4.3) is based on the primary endpoint ‘change in total score of DCL-ADHS from T2 (after TAU-stabilisation) to T3 (after experimental or control treatment; 12 weeks)’ using the two-sided t test with a power of 80% at a significance level of 5%. Studies on psychosocial interventions on the treatment of ADHD report effect sizes of about *d* = 0.8 [100], where *d* denotes the difference in the change score between the two randomised groups in standard deviation units. However, we have chosen a smaller effect size to calculate the sample size because recent meta-analyses referring to less biased outcome criteria such as assessments by clinicians report smaller effects of non-pharmacological interventions for the treatment of ADHD [22]. Furthermore, these effect sizes are based on trials with mostly waiting control group, thus, we expect our effects to be smaller. Additionally, in our highly affected clinical sample treatment effects might be less pronounced. A smaller effect size also accounts for the fact that the planned intention-to-treat approach might dilute the true expected effect – patients who discontinue therapy will be included in the primary analysis. We assume low to zero pre-post effects within our control group. Therefore, an effect size of *d* = 0.5 between groups seems realistic, and it is considered to be still clinically relevant. To detect a difference assuming the true effect size is *d* = 0.5, 64 patients with non-missing data per group are required (critical *t* = 1.98, *df* = 126). In order to account for the possibility that a few patients (8%) will have incomplete data at T3, in total 140 patients will have to be randomised. Studies on psychosocial interventions in ADHD children and their parents report attrition rates ranging from 5 to 20%. The study by Antshel et al. on CBT for adolescents with ADHD-symptoms unresolved by medication fits best with our intended sample. In this trial CBT adherence was good (all patients attended 13–16 sessions with half of the patients never missing an appointment and half missing between one and three appointments). Therefore, a rate of 8% with incomplete data at T3 seems conservative [23].

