#### Analysis of primary endpoint

The primary statistical analysis will be by intention-to-treat, so that all randomised patients will be analysed according to their allocated arm. Changes in the DCL-ADHS score from T2 to T3 and T2 to T4, respectively, will be evaluated in a linear regression model including treatment, centre, visit and the respective T2-baseline DCL-ADHS. Further covariates predictive of missingness will be included based on a pre-specified selection strategy to correct for potential bias arising from missing data. The primary treatment comparison of the change score at T3 will be based on least-squares means with a two-sided 95% confidence interval. Other possibly relevant covariates may be considered as well. Subgroup analyses will be conducted in an exploratory manner by inclusion of interaction terms in the linear regression model. They will focus on the analysis of patients’ and parents’ comorbidities. In addition, gender effects will be investigated as prognostic and predictive factors.

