JTCI: German questionnaire ‘Junior Temperament und Charakter Inventar’ to assess child personality
KIDSCREEN-10: The Health-Related Quality of Life Questionnaire for Children and Young People
MID: Monetary incentive delay task
MMRM: Mixed-effects model for repeated measures
MRI: Magnetic resonance imaging
ODD: Oppositional defiant disorder
PP: Per protocol population
RCT: Randomised controlled trial
SBB-ADHS: Selbstbeurteilungsbogen für Aufmerksamkeitsdefizit-/Hyperaktivitätstörungen
SBB-SSV: Selbstbeurteilungsbogen für Störungen des Sozialverhaltens
SOP: Standard operating procedures
SRS: Social Responsiveness Scale
SST: Stop Signal Task
STAND: Supporting Teens’ Academic Needs Daily
Step 1: Observational period of 4 weeks
Step 2: Main treatment period with a duration of 12 weeks
T0: Screening at the beginning of the study to assess inclusion and exclusion criteria
T0/T1: To indicate overlap in diagnostic procedure of T0 and T1 assessment
T1: Assessment at baseline before Step 1
T2: Assessment at the end of Step 1 and before beginning of Step 2 intervention
T3: Assessment at the end of Step 2 intervention
T4: Follow-up assessment 12 weeks after the end of Step 2 intervention
TASH: Telephone-assisted self-help for parents
TAU: Treatment as usual, observation phase between T1 and T2
TCS: Transcranial sonography
VER: German questionnaire ‘Verhalten in Risikosituationen’ to assess the perceived ability to solve difficult parenting situations
WFIRS-P: Weiss Functional Impairment Rating Scale – parent report
WNV: Wechsler Nonverbal Scale of Ability, tool for assessment of the inclusion criterion intelligence level
WURS-K: Wender Utah Rating Scale, short version
YSR: Youth Self Report Scale

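### The primary model lists visit but no treatment-by-visit term, so fitted jointly it does not isolate the promised T3 comparison

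*Protocol article*

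**What the plan says.** In the protocol article, *Primary outcome* fixes a single time window: "The primary endpoint is the change in ADHD symptoms from T2 to T3". The sample size section is built on the same change score. It uses a two-sided t test, a standardised difference of which it says "0.5 between groups seems realistic, and it is considered to be still clinically relevant", and the result that "64 patients with non-missing data per group are required".

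*Analysis of primary endpoint* takes two responses, the change to T3 and the change to T4, joined by the word respectively. These "will be evaluated in a linear regression model including treatment, centre, visit and the respective T2-baseline DCL-ADHS". Two sentences later: "The primary treatment comparison of the change score at T3 will be based on least-squares means with a two-sided 95% confidence interval". Interaction terms appear in that section only for exploratory subgroup analyses.

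The hypotheses at the end of *Background* include: "We expect treatment effects and group differences to remain stable at follow-up". The abbreviation list contains "MMRM: Mixed-effects model for repeated measures", but the article text does not use the term. The abstract also describes the primary analysis as linear regression.

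**The concern.** A visit term does something only when T3 and T4 rows sit in the same model. In that model, with visit as a main effect and no treatment-by-visit term, one treatment coefficient serves both visits. The least-squares means at T3 then differ between arms by exactly the same amount as those at T4. The comparison labelled T3 therefore draws equally on follow-up data, although follow-up is outside the primary endpoint and outside the sample size calculation.

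Two things are at stake. If the effect fades or grows after treatment ends, the headline result no longer describes the end of treatment. The model also assumes that the group difference is constant from T3 to T4, so it cannot be used to examine the stability hypothesis. *Analysis of secondary endpoints* says that the continuous secondary measures at T3 are handled similarly to the primary one, so the ambiguity carries over to them.

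**Working it through.** **1. The plan's own figure.** Inputs: d = 0.5, two-sided 5%, 80% power (*Proposed sample size and power calculations*). The exact noncentral t gives power 0.8015 with 64 per arm (df 126, critical t 1.979) and 0.795 with 63. Then 128 / 0.92 = 139.1, which rounds up to 140. The stated 64 per group and 140 randomised are reproduced. This calculation concerns the T3 change alone.

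**2. What the listed terms estimate when fitted jointly.** Write the model as change = treatment + centre + visit + T2 score. The treatment difference in least-squares means is the single treatment coefficient at either visit. With complete data and equal variances it estimates (effect at T3 + effect at T4) / 2:
- T3 0.5, T4 0.5: (0.5 + 0.5) / 2 = 0.50
- T3 0.5, T4 0.25: (0.5 + 0.25) / 2 = 0.375
- T3 0.5, T4 0: (0.5 + 0) / 2 = 0.25

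The averaging does not depend on the covariance structure. A mixed model with the same fixed effects would still give one common difference.

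**3. Standard error, only if rows are treated as independent.** Assume residual SD 1 at each visit, 64 per arm and a T3-T4 residual correlation rho, which the document does not give.
- Variance assumed by the model: 2 / (2 × 64) = 1/64, so SE = 0.125.
- True variance: the mean of a patient's two rows has variance (1 + rho) / 2, so the difference between arms has variance (1 + rho) / 64.
- Ratio of true to model SE: sqrt(1 + rho).
- Two-sided type I error: 2 × [1 − Phi(1.96 / sqrt(1 + rho))].

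| Assumed rho | SE ratio | CI width, % of correct | Type I error | Simulated |
|---|---|---|---|---|
| 0.3 | 1.14 | 88 | 8.6% | 8.5% |
| 0.5 | 1.22 | 82 | 11.0% | 11.6% |
| 0.7 | 1.30 | 77 | 13.3% | 12.7% |

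**4. Simulation.** Settings: 64 per arm, six centres, a baseline covariate, complete data, 4,000 runs per scenario, rho 0.3 to 0.7. The pooled main-effects model with independent errors and a true T3 effect of 0.5 gave:

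| T4 effect | Mean estimate | Coverage of the T3 effect | Rejection rate |
|---|---|---|---|
| 0.5 | 0.50 | 87–92% | 94–96% |
| 0.25 | 0.37–0.38 | 76–80% | 79–82% |
| 0 | 0.25 | about 50% | 50–51% |

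Coverage and rejection here combine the averaging with the independence assumption. The estimates reflect the averaging alone.

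**5. After correction.** In the same scenarios:
- Adding treatment-by-visit gave T3 estimates of about 0.50, coverage of 94–95%, type I error of about 5% and power of about 0.80, even with errors left independent.
- A T3-only ANCOVA gave about 0.50, 94–96%, 4–5% and about 0.80.

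Both match the power the plan was sized for.

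**The case against.** The strongest reply has four parts.

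First, the word respectively can mean one regression per time point. The T3 analysis is then an ordinary ANCOVA with one row per patient, with no mixing of visits and no repeated rows. This stands. On that reading the only fault is that visit is constant within each model and cannot be estimated, so the word must go. The text does not say which reading is meant.

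Second, the list of terms is introduced as what the model includes and need not be complete, and naming a T3 contrast suggests that an interaction was intended. That is fair as evidence of intent. But the section does name the terms, and it mentions interactions only for subgroups. The listed terms and the promised contrast do not fit together in a joint model, and this is a matter of what is stated, not of detail left to an unseen analysis plan.

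Third, a reader might infer that the model ignores within-patient correlation and that the type I error is therefore 11% to 13%. The document does not support this. It is silent on covariance, which is commonly left to the SAP. The MMRM entry among the abbreviations suggests that a repeated-measures model may have been intended. The correlation is also not given. The inflation needs joint fitting, no interaction, independent errors and positive correlation all at once.

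Fourth, if the group difference really is stable, the pooled estimate is unbiased for T3. This is true, but stability is one of the trial's own hypotheses and should not be built into the primary estimate. The article also says that T2-to-T4 changes will be evaluated for all endpoint scores, so stability may still be examined in another analysis. What is lost is the possibility of examining it in this model.

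**Conclusion.** The primary model statement needs correction on either reading. Fitted jointly with the listed terms, it does not isolate the T3 effect. It reports a T3/T4 average: 0.375 or 0.25 in place of 0.5 SD when the T4 effect is 0.25 or 0, given complete data and equal variances. Fitted separately, the T3 analysis is valid and only the redundant visit term is wrong.

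It would go too far to say that the plan cannot deliver a T3 comparison. A T3 contrast can be computed, and it is unbiased if the group difference is constant between visits. It would also go too far to call the confidence interval too narrow without conditions. That follows only if the two rows per patient are treated as independent in the pooled model, and then type I error is 8.6%, 11.0% and 13.3% for assumed correlations of 0.3, 0.5 and 0.7. The planned 140 randomised patients are not affected.

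**What to change.** Replace the model sentence with one of two explicit statements:

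- **(a) Repeated-measures model.** Changes at T3 and T4 are analysed with treatment, visit, treatment-by-visit, centre and T2 DCL-ADHS, with an unstructured within-patient covariance. The treatment contrast at T3 is primary. The T4 contrast, and the difference between the T3 and T4 contrasts, are secondary and address stability.
- **(b) Separate models.** The primary analysis is an ANCOVA of the T3 change with treatment, centre and T2 DCL-ADHS, without visit. T4 has its own model.

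Under (a), a baseline-by-visit term and Kenward-Roger degrees of freedom are good practice but are not needed for the correction. The same choice should be stated for the continuous secondary endpoints that follow the primary analysis.

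The cost is one sentence in the protocol, a matching check of the SAP, and a few lines of SAS code. No new data and no change in sample size are needed.

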#### Analysis of secondary endpoints

Secondary endpoints will be analysed descriptively in a similar fashion as the primary outcome, using regression models as appropriate for the respective type of data. Treatment effects will be calculated with two-sided 95% confidence intervals. Details are specified in a statistical analysis plan which was prepared before the inclusion of the first patient. For all endpoint scores the change between T2-baseline and T3, and T2 and T4 will be evaluated. The analysis of the change between T2-baseline and T3 will be done similar to the analysis of the primary endpoint for continuous measurements. The difference in CGI between T2 and T3 will be analysed using the Mann-Whitney-*U*-test. The difference in CGI between T2 and T4 will be analysed using a Kruskall-Wallis test. Possible moderators and mediators of the DCL-ADHS score will be analysed using linear regression.

## Discussion

Adolescence is a crucial period for determining patients’ life trajectories in terms of mastering educational and psychosocial developmental tasks. However, in adolescents with ADHD motivation to seek treatment, treatment adherence and compliance are often lacking [15]. Furthermore, comorbidities gain importance; however, this is often not adequately addressed by standard psychological and pharmacological interventions for ADHD. Psychopharmacological treatment is of limited effect in this age group [12, 14]. Thus, there is a strong need for effective psychosocial interventions that generate high motivation and compliance and that also take into account non-core ADHD symptoms, such as emotion regulation and self-image, as well as comorbidity. Considering the limited empirical evidence for non-pharmacological treatment options of ADHD in adolescence, ESCAadol is conceptualised as a RCT for the evaluation of an innovative short-term CBT programme tailored to the needs of ADHD patients aged 12 to 17 years. One limitation of the trial is the absence of a waiting control group under routine clinical care. However, considering the limited number of potential participants in that age group, limiting the study design to two groups seemed necessary for obtaining a sufficient sample size. Therefore, we decided on an active control treatment to provide at least minimal support for adolescents in that crucial period for ethical reasons. Furthermore, demonstrating superiority of a short-term behavioural therapy programme over an active control condition presents a more rigorous test of the treatment efficacy than comparing it to no intervention. This RCT will be conducted in accordance with the highest standards of psychotherapy research, employing blinded outcome ratings and relying on power analyses to ensure adequate statistical power to detect effects. All raters and therapists receive special training prior to being involved with the study. The main treatment comprises a manualised therapy. Adherence to the manual will be checked. We compare the efficacy of this adolescent-centred intervention with a parent-centred telephone-assisted self-help programme as an active control treatment. Taking into account the broad spectrum of clinical presentations, comorbidities and environmental factors, the study furthermore aims at achieving a sample size that allows for the identification of predictors of treatment response across different modalities (psychometric variables, neuropsychological tests, brain functioning during rest and cognitive activity, structural brain imaging and biomarkers in blood and saliva). Results aim to fill a knowledge gap in the treatment of adolescents with ADHD who do not benefit from routine clinical care and at evaluating a cost-effective and feasible individualised treatment that can easily be implemented in routine clinical practice within the context of a personalised medicine approach.

### Trial status

Recruitment for this trial is ongoing.

## Abbreviations

ADHD: Attention-deficit/hyperactivity disorder
ADHS-SB: German self-rating scale ‘ADHS-Selbstbeurteilungsskala’ to assess parental ADHD
ARI: Affective Reactivity Index
BAS: Behavioural Activation Systems
BAT: Behavioural Avoidance Test
BIS: Behavioural Inhibition Systems
BT: Behavioural therapy
CBCL/6–18: Child Behaviour Checklist for ages 6–18 years
CBT: Cognitive behavioural therapy
CD: Conduct disorder
CGI: Clinical Global Impression
CNV: Contingent negative variation
CPT-OX: Variant of the continuous performance task
CRA: Clinical research associate
DASS: Depression Anxiety Stress Scales
DCL-ADHS: German clinical checklist ‘Diagnose-Checkliste Aufmerksamkeitsdefizit-/Hyperaktivitätsstörung’ to assess ADHD symptoms and impairment
DCL-SSV: German Clinical Checklist ‘Diagnose-Checkliste für Störungen des Sozialverhaltens’ to assess symptoms and impairment of disruptive behaviour disorders and related problems
DMC: Data Monitoring Committee
DRKS: German Clinical Trials Register
DSM-5: *Diagnostic and Statistical Manual of Mental Disorders, Fifth Edition* (DSM-5), Classification and diagnostic tool for mental disorders issued by the American Psychiatric Association
EEG: Electroencephalography or electroencephalogram
ESCAadol: Acronym for the study ‘Evidence-based stepped care of ADHD: individualised short-term therapy for adolescents impaired by ADHD despite previous routine care treatment’
FAI: Family Adversity Index
FAS: Full Analysis Set
FB-Ä: German questionnaire ‘Elternfragebogen zum Umgang mit Ärger’ to assess parental aggression
FBB-ADHS: German Observer Rating Scale ‘Fremdbeurteilungsbogen für Aufmerksamkeitsdefizit /Hyperaktivitätsstörung’ to assess ADHD symptoms and impairment
FBB-SSV: German Observer Rating Scale ‘Fremdbeurteilungsbogen für Störungen des Sozialverhaltens’ to assess symptoms and impairment of disruptive behaviour disorders and related problems
FEEL-KJ: Questionnaire for the assessment of emotional dysregulation in children and adolescents
FPNE: German questionnaire ‘Fragebogen zum positiven und negativen Erziehungsverhalten ’ to measure negative parenting practices
FZEV: German questionnaire ‘Fragen zum Erziehungsverhalten’ to measure positive, reinforcing and promotive parenting practices
ICH-GCP: Good Clinical Practice
IMTP: Individualised Modular Treatment Programme, short-term behaviour therapy programme comprising 10 sessions specifically developed for adolescents with ADHD
IQ: Intelligence quotient
JTCI: German questionnaire ‘Junior Temperament und Charakter Inventar’ to assess child personality
KIDSCREEN-10: The Health-Related Quality of Life Questionnaire for Children and Young People
MID: Monetary incentive delay task
MMRM: Mixed-effects model for repeated measures
MRI: Magnetic resonance imaging
ODD: Oppositional defiant disorder
PP: Per protocol population
RCT: Randomised controlled trial
SBB-ADHS: Selbstbeurteilungsbogen für Aufmerksamkeitsdefizit-/Hyperaktivitätstörungen
SBB-SSV: Selbstbeurteilungsbogen für Störungen des Sozialverhaltens
SOP: Standard operating procedures
SRS: Social Responsiveness Scale
SST: Stop Signal Task
STAND: Supporting Teens’ Academic Needs Daily
Step 1: Observational period of 4 weeks
Step 2: Main treatment period with a duration of 12 weeks
T0: Screening at the beginning of the study to assess inclusion and exclusion criteria
T0/T1: To indicate overlap in diagnostic procedure of T0 and T1 assessment
T1: Assessment at baseline before Step 1
T2: Assessment at the end of Step 1 and before beginning of Step 2 intervention
T3: Assessment at the end of Step 2 intervention
T4: Follow-up assessment 12 weeks after the end of Step 2 intervention
TASH: Telephone-assisted self-help for parents
TAU: Treatment as usual, observation phase between T1 and T2
TCS: Transcranial sonography
VER: German questionnaire ‘Verhalten in Risikosituationen’ to assess the perceived ability to solve difficult parenting situations
WFIRS-P: Weiss Functional Impairment Rating Scale – parent report
WNV: Wechsler Nonverbal Scale of Ability, tool for assessment of the inclusion criterion intelligence level
WURS-K: Wender Utah Rating Scale, short version
YSR: Youth Self Report Scale
